### Assignment of interventions and unblinding

Enrolled iHEU will be block-randomized in a 1:1 ratio to receive 8 × 10^9^ CFU of *B. infantis* Rosell®-33 or placebo daily from postpartum day 1–3 to 28–30. Randomization will be done by a statistician and the confidential randomization list will be provided to the pharmacist. The intervention and placebo products will be packaged in identical sachets with identical labelling. Participants, care providers, investigators and outcome assessors will be blinded to the participant’s allocated intervention.

Unblinding will occur if there is concern raised by the investigators or other clinical care providers, and they believe that unblinding would change the care provided. Unblinding might be requested from the human ethics committees, Data Safety and Monitoring Board (DSMB) or the sponsor. Unintentional unblinding will be recorded as study deviation.

### Adherence monitoring

Adherence will be encouraged and assessed using three measures: (i) self-report with daily record of administration using diaries and 1-day, 7-day and 2- or 4-week recall at the Day 10–14 and week 4 visits, respectively, (ii) return of empty sachets, (iii) and *B. infantis* Rosell®-33 Real-Time qPCR to assess absolute abundance in infant stool. We will triangulate self-report, sachet count and absolute *B. infantis* Rosell®-33 abundance in infant stool to assess adherence.

### Use of concomitant medication during the trial

Concomitant medications can be prescribed to infants as per the standard of care as necessary and will be recorded. However, mothers will be asked to not give their infants non-study probiotics or prebiotics during the study period.

### Participant timeline, data and sample collection

Participants will be followed from birth to 9 months of life, as outlined in the schedule of events (Table 1). Data and sample collection will be done by clinical staff. Upon enrolment, infants will be randomized to receive *B. infantis* Rosell®-33 or placebo for the first 4 weeks of life, starting on day 1–3 of life. Follow-up visits will be conducted at 10–14 days (for safety assessment and adherence monitoring and support), week 4 (end of the intervention), and weeks 7, 15, 24 and 36 of life, with adverse event solicitation, extensive questionnaires, anthropometrics, examinations, and sample collection performed (Table 1). Participant retention will be promoted through regular phone calls and messages. Maternal CD4 count and HIV viral load and infant HIV PCR test results will be accessed by the study coordinator from the National Health Laboratory Service password-protected web-based interface. An additional HIV DNA PCR will be performed at the Day 10–14 visit to ensure no missed HIV transmissions during labour. Any infant with a positive HIV DNA PCR will discontinue product. Maternal physical examination will include height, weight, and blood pressure. Infant physical exam will include an assessment of birth defects, anterior fontanelle, palette, heart sounds, abdominal masses, hip click, external genitalia, and sacral dimple at enrolment. Thereafter, length, weight and head circumference will be measured at each visit and a targeted exam for any symptoms. Infant health status will be assessed at each visit by interview and medical folder review using standardized forms. Detailed feeding questionnaires are used that have been validated in our and other similar settings [49]. At each visit, infant stool is collected taking care to avoid the diaper, placed at -20 °C, and transferred to the laboratory within 6 h to be stored at -80 °C. Infant blood will be collected at enrolment, week 4, 7, 15 and 36 and used for whole blood assay or PBMC will be extracted and stored on LN_2_ and plasma stored at -80 °C. Maternal blood, stool, vaginal swabs and breastmilk will be collected at week 4, 15 and 36 and biobanked for future studies (Table 1).

### Outcomes and statistical methods

#### Primary outcomes

Analyses will follow intention-to-treat (ITT) principles comparing the two randomised groups.We will compare Alpha (Shannon) and Beta (Bray Curtis and UniFrac) diversity metrics, calculated from shotgun metagenomic sequencing data for each infant stool sample, between treatment arms at 4 weeks. Cross-sectional abundance differences for taxa and functional genes will be assessed using DeSeq2 (negative-binomial) [50] or Corncob (beta-binomial) [51] regression models, with the Benjamini–Hochberg multiple-test correction on the resulting *p*-values (to control the false-discovery-rate (FDR)) [52]. Regressions will be adjusted for confounders, like sex, weight, and feeding mode.Markers of intestinal inflammation and microbial translocation at baseline, weeks 4, 7 and 36: We will compare markers of intestinal inflammation and microbial translocation (Lipocalin-2 (Lcn-2), soluble CD163 (sCD163), iFABP and lipopolysaccharide binding protein (LBP) measured by ELISA in infant plasma) cross-sectionally at each time point between groups using Mann–Whitney U tests. We will correlate absolute concentrations of *B. infantis* in the fecal microbiome with these markers. We will use a mixed-effects regression (MER) modeling approach to account for repeated measurements and for relevant covariates like feeding status and sex.BCG-specific total net Th1 cytokine producing cells at 7 weeks of life: We will compare frequencies of total net cytokine producing cells in response to stimulation with BCG between arms at weeks 7 using linear regression after adjusting for confounders, like sex, weight, and feeding mode. Additionally, T cell response data will be analyzed by COMPASS [53] to compute a ‘functionality score’ or ‘polyfunctionality score’. This analysis will be a regression model testing the association between functionality or polyfunctionality scores and iHEU (*B. infantis* versus placebo). We will perform two-sided hypothesis testing with alpha = 0.05. If the model shows a significant result (*p* < 0.05), we will perform a series of univariate analyses in which we test for an association between a particular functional profile and arm. Those profiles identified as significantly associated will be incorporated into a multivariate linear regression model, which will include two-way interaction terms. This will allow us to create a model that includes the cytokine-producing profiles that are most associated with the intervention. We will test the classification accuracy of this model using receiver-operative curve (ROC) analysis. In all models, we will include sex, birth weight, and feeding mode as possible confounders.

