### Trial design

This is a two-arm, randomized, double-blinded, placebo-controlled trial of *B. infantis* Rosell®-33 supplementation in the first 4 weeks of life in 200 breastfed iHEU. iHEU will be block-randomized in a 1:1 ratio to receive ~ 8 × 10^9^ CFU of *B. infantis* Rosell®-33 versus placebo daily from postpartum day 3 to 28. Participants will be followed over 9 months. Assessment of infant outcomes and sample collection will be done at birth, day 10–14 and weeks 4, 7, 15, 24 and 36 of life (Table 1).

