For this trial, Lallemand Health Solutions will manufacture the investigational product containing 8 × 10^9^ CFU *B. infantis* Rosell®-33 per dose (single microbial active ingredient) and carrier material (maltodextrin), as well as the placebo (containing all materials besides *B. infantis* Rosell®-33). Mothers will be provided with two 14-day supplies of identical looking 1 g sachets containing either *B. infantis* Rosell®-33 or the placebo powder at enrolment and the first follow-up visit, both of which can be stored at room temperature. Mothers will be requested to pour one sachet (containing the investigational product or placebo) into a provided sterile cup daily, add 2 mL of expressed breastmilk, mix the powder and breastmilk, and then cup-feed her infant immediately. If, for any reason, the mother is unable to produce any/enough breastmilk during the intervention phase and is therefore using infant formula, she will be advised to mix the sachet with formula.

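### Objective 1 is tested at the end of dosing without separating the supplemented strain, so product DNA alone can make the *B. infantis* and beta-diversity results positive

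*Protocol article*

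**What the plan says.** All references are to the Protocol article.

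- **Endpoint.** Under Primary outcomes, Shannon, Bray-Curtis and UniFrac are "calculated from shotgun metagenomic sequencing data for each infant stool sample, between treatment arms at 4 weeks". Taxa and functional genes are compared by DESeq2 or Corncob with false-discovery-rate control.
- **Timing.** Participant timeline, data and sample collection lists the visits as "week 4 (end of the intervention), and weeks 7, 15, 24 and 36 of life". It adds: "At each visit, infant stool is collected taking care to avoid the diaper".
- **Dosing.** Assignment of interventions and unblinding gives dosing as "daily from postpartum day 1–3 to 28–30". Trial design gives "versus placebo daily from postpartum day 3 to 28". The Intervention section states 8 × 10⁹ CFU per dose, a single strain, and "Mothers will be provided with two 14-day supplies of identical looking 1 g sachets".
- **The same signal used elsewhere.** Adherence monitoring uses qPCR of the strain in stool, together with diaries and sachet counts, to judge whether the product was taken. Exploratory outcomes compare that qPCR between arms.
- **Stools after dosing.** Composition over nine months is a secondary outcome.
- **Planning values.** Sample size says that 100 per group can detect a twofold abundance difference and a PERMANOVA R² of 0.01 or higher. It draws partly on *B. infantis* copy numbers.

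**The concern.** At week 4, one arm has just been given a live organism every day for about four weeks and the other has not. Sequencing a stool counts three things together: product passing through, product that has colonised, and the rest of the community. The first is evidence of swallowing, and the protocol itself uses it as evidence of adherence. If it also enters the distance matrices and the *B. infantis* test, a significant Objective 1 result can arise with nothing else in the gut altered.

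What is at stake is the interpretation. The hypothesis in the Background is that supplementation brings beneficial changes in microbiome composition and function. As the analysis is laid out, a positive week-4 result cannot say whether the community beyond the product changed.

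**Working it through.** **1. The plan's own figure.** The Objective 1 calculation cannot be reproduced. The article gives no power level, overdispersion or community data for its beta-binomial simulation. The twofold difference and R² = 0.01 are used here only as yardsticks.

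**2. Timing.** Two 14-day supplies give 2 × 14 = 28 daily sachets. A start on day 1 ends on day 1 + 27 = 28, and a start on day 3 ends on day 30. This matches the day 28-30 end in one section. The other section's day 3 to 28 is 28 − 3 + 1 = 26 days. On either reading, the week-4 stool falls on or within days of the last doses. (The visit schedule in Table 1 is not shown.)

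**3. How little product doubles the *B. infantis* share.** The plan gives 3000 copies per 2.5 ng DNA (day 4-7 of life). Assume a mean genome of G = 2-5 Mb, 650 g/mol per base pair, one copy per genome, and all DNA bacterial.
- Genomes in 2.5 ng = 2.5×10⁻⁹ × 6.022×10²³ / (G × 650) = 1,158,077 (2 Mb) to 463,231 (5 Mb).
- Baseline share b = 3000 / genomes = 0.26% to 0.65%.
- Solving b(1 − f) + f = 2b gives f = b/(1 − b) = 0.26% to 0.65%.

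A product share below 1% would double the mean of that taxon.

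**4. What the share might be.** Transit share = 8×10⁹s / (8×10⁹s + L·g). All of the following are assumed: L = 10⁹ to 10¹¹ bacteria per gram, g = 5 to 50 g of stool per day, and s = 1% to 100% of product DNA recovered. The result runs from 0.002% to 62%. On a grid of 27 combinations, 7 exceed 2% and 5 exceed 5%. These counts are not probabilities.

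**5. Simulation with no change except the product.** Loss of 2.5% by week 7 leaves 195 infants, so 97 per arm. The background is 60 Dirichlet taxa plus a low-level resident *B. infantis*, with the same distribution in both arms. Product reads are added in the active arm only, with a Beta-distributed share of mean f. There are 199 permutations and 100 replicates per cell. The *B. infantis* test is a Bonferroni-corrected rank test standing in for DESeq2 or Corncob. Paired entries are for Dirichlet concentration 6 / 20.

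| f | R² | Bray-Curtis rejection | *B. infantis* rejection | Bray-Curtis, *B. infantis* removed |
|---|---|---|---|---|
| 0 | 0.0053 / 0.0054 | 10% / 5% | 0% / 0% | 9% / 5% |
| 0.4% | 0.0051 / 0.0052 | 3% / 6% | 9% / 9% | 4% / 5% |
| 2% | 0.0065 / 0.0074 | 13% / 26% | 100% / 100% | 5% / 4% |
| 5% | 0.0128 / 0.0154 | 94% / 99% | 100% / 100% | 8% / 5% |
| 10% | 0.0306 / 0.0399 | 100% / 100% | 100% / 100% | 6% / 7% |

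The Monte Carlo standard error near 5% is √(0.05 × 0.95/100) = 2.2 points.

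A second simulation, with a different assumed community (placebo Shannon about 1.5, 120 replicates), gave R² about 0.03 and 100% rejection at f = 5%. With product reads removed, rejection was 2-8%. UniFrac and functional genes were not simulated.

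**6. Shannon.** Adding a new taxon at fixed share f to a community with Shannon H changes it by h(f) − fH, where h(f) = −f ln f − (1 − f) ln(1 − f). For H = 1.5:
- f = 5%: 0.199 − 0.075 = +0.12.
- f near 46%: zero, and negative above that.

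In the tabulated simulation the mean difference was +0.042 / −0.016 at f = 10% and −0.207 / −0.441 at f = 40%. The sign depends on the community and the share, so no Shannon rejection rate is given.

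**The case against.** The strongest reply is that carriage is the point. The Objectives section asks about the effect on gut microbiome composition and diversity and does not restrict this to the resident community. The Background builds its case on depleted *Bifidobacteria* in these infants and on *B. infantis* abundance tracking BCG responses. A gut enriched in *B. infantis* at week 4 is thus part of the intended effect, and deleting those reads would change the estimand. This stands, and it is why the all-reads analysis should remain primary.

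A reader might infer that the primary result is bound to be positive, or that it would show only that the sachet was swallowed. The documents support neither:
- The product's share of reads is not given. At 0.4% the PERMANOVA behaves as under the null.
- No single success rule for Objective 1 is stated.
- The per-taxon tests name which taxa differ, and strain qPCR measures recovery separately.
- The plasma markers and BCG responses, the other primary outcomes, are not read from stool DNA.
- Dilution would make other taxa appear twofold lower only if product filled half of all reads. At f = 5% they fall by a factor of just 0.95.

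It can also be said that strain filtering may be set out in the full protocol or analysis plan, neither of which is shown. That is possible, and silence in an article is not in itself an error. The point here is that the time point and metrics the article does fix cannot by themselves separate passage of the product from a wider change.

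**Conclusion.** The concern holds in a limited form. Product DNA at week 4 can make the *B. infantis* taxon test and the beta-diversity tests positive when nothing else differs. From a share of about 5% of reads this is nearly certain for Bray-Curtis in the simulated settings, with an R² above the 0.01 the trial is sized for. For the *B. infantis* taxon, 2% is enough. Because rejection is near nominal once those reads are removed, the signal comes from the product.

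The percentages rest on assumed communities, on read share following genome share, and on a rank test in place of the planned models. Whether the actual share reaches these levels cannot be told from the documents. The all-reads comparison is a valid estimate of the total effect. The weakness lies in what may be concluded from it about the rest of the microbiome. This is a worthwhile, inexpensive improvement and does not invalidate the primary analysis.

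**What to change.** 1. Keep the all-reads week-4 comparison as the primary analysis, described as the total effect including carriage of the product.
2. Pre-specify beside it the same diversity, PERMANOVA and differential-abundance analyses with reads of the supplemented strain removed and profiles renormalised. If the strain cannot be resolved, remove all *B. infantis*.
3. State that a change in the microbiome beyond the product will be claimed only if the strain-removed analysis supports it.
4. Name the stools already collected from week 7 onward as supporting evidence of persistence. The Background notes that co-trimoxazole is recommended from 6 weeks of age, so these samples may be affected by it and should be interpreted accordingly.
5. Reconcile the dosing days in Trial design with those in Assignment of interventions and unblinding, so that the week-4 stool can be placed relative to the last dose.

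The cost is one bioinformatic rerun and a few sentences in the protocol or analysis plan, with no new samples or visits. The drawback is that removing all *B. infantis* also removes any resident *B. infantis*, so both versions must be reported.

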## Methods and design

### Objectives

The primary objectives of this study are to evaluate the effect of early-life *B. infantis* Rosell®-33 supplementation in iHEU on gut microbiome composition and diversity (objective 1), and markers of intestinal inflammation and microbial translocation (objective 2) at 4 weeks of life, and the effect on Th1 cytokine responses to BCG at 7 weeks of life (objective 3).

The secondary objectives of this study are to evaluate the effect of *B. infantis* Rosell®-33 supplementation on longitudinal succession of the gut microbiota composition, diversity and function, stool metabolome and T cell subset ontogeny during the first 9 months of life.

Exploratory objectives are to evaluate whether *B. infantis* Rosell®-33 supplementation improves infant growth, vaccine responses (including antibody titres) to other early childhood vaccines, all-cause morbidity or neurodevelopment during the first 9 months of life.

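### Objective 2 is set at week 4, but its primary outcome spans four visits and four markers, with no lead visit, lead marker, deciding analysis or stated error control

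*Protocol article*

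**What the plan says.** All places are in the protocol article.

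- **Objectives:** the second primary objective concerns "markers of intestinal inflammation and microbial translocation (objective 2) at 4 weeks of life". One visit is named.
- **Primary outcomes, second item:** the outcome is headed "Markers of intestinal inflammation and microbial translocation at baseline, weeks 4, 7 and 36". The markers are "Lipocalin-2 (Lcn-2), soluble CD163 (sCD163), iFABP and lipopolysaccharide binding protein (LBP) measured by ELISA in infant plasma". They are compared "cross-sectionally at each time point between groups using Mann–Whitney U tests".
- **Same item, second analysis:** "We will use a mixed-effects regression (MER) modeling approach to account for repeated measurements and for relevant covariates like feeding status and sex". The infant's enrolment value is not named as a covariate, and neither analysis is called the main one.
- **Error control:** the first primary item (taxa and functional genes) is analysed "with the Benjamini–Hochberg multiple-test correction on the resulting" p-values. Secondary outcomes applies an FDR correction to metabolites. Exploratory outcomes applies one to Mann–Whitney tests of strain abundance at each time point. The second primary item mentions none. The sentence "We will perform two-sided hypothesis testing with alpha = 0.05" appears in the third primary item, on BCG responses.
- **Sample size:** objective 2 is sized on iFABP alone, with no allowance for several tests.
- **Participant timeline, data and sample collection:** "Infant blood will be collected at enrolment, week 4, 7, 15 and 36". An enrolment value is therefore available for adjustment.

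**The concern.** The other two primary items keep the single visit named in their objectives (week 4 for the microbiome, week 7 for BCG). Only objective 2 changes, from one visit to four. A reader of the results could not tell whether a difference at week 7 or week 36 but not at week 4 meets the objective. Nor could they tell which marker counts, or which result prevails if the rank test and the mixed model disagree.

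The four baseline comparisons answer no trial question: before treatment, any difference between randomised arms is chance. The cross-sectional tests also make no use of the infant's enrolment value. As stated, a primary outcome has less protection against chance findings than an exploratory outcome analysed with the same kind of test.

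**Working it through.** **1. The plan's own figure.** Inputs from Sample size: mean log iFABP 0.454, SD 0.164, a 20% difference, 80% power, 51 per group. I assume two-sided alpha 0.05, because that level is stated only in the BCG item.

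- Difference: 0.2 × 0.454 = 0.0908. Standardised: 0.0908 / 0.164 = 0.554.
- n per group = 2 × [(1.960 + 0.842) × 0.164 / 0.0908]² = 51.2 (52.2 by the t-test). The stated 51 is reproduced to rounding. It covers one marker and one test.

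**2. Count of tests.** 4 markers × 4 visits = 16; after baseline, 4 × 3 = 12; at week 4 only, 4.

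**3. Chance of at least one nominal p<0.05 with no effect.** If the tests are independent, this is 1 − 0.95^k. For correlated tests I simulated null z-statistics. The document gives no correlations, so these are assumed; for two different markers at two different visits, the correlation is the product of the two values.

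| Correlation between markers / between visits | 16 tests | 12 post-baseline | 4 at week 4 |
|---|---|---|---|
| 0 / 0 | 56% | 46% | 19% |
| 0.3 / 0.5 | 47% | 39% | 17% |
| 0.5 / 0.5 | 43% | 36% | 16% |
| 0.7 / 0.7 | 31% | 27% | 13% |

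The 12-test column is the relevant one for the four-visit outcome, since a baseline difference cannot support a claim of effect. The last column applies if the trial is held to the visit in its objective.

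**4. Cost of control.** The plan expects 195 infants at week 7; I use 97 and 98 per arm.

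- Noncentrality: 0.554 × √(97 × 98 / 195) = 3.87.
- t-test power for iFABP: 97% at alpha 0.05, and 91% at 0.05 / 4 = 0.0125 (the first Holm step).
- With a Mann–Whitney test at relative efficiency 0.955 and 97 per arm, power at 0.0125 is about 90%.
- The document gives no mean, SD or target difference for Lcn-2, sCD163 or LBP, so their power cannot be computed. The iFABP figures come from day 4–7 samples, not week 4.

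**5. Value of baseline adjustment.** The gain equals 1/(1 − ρ²) − 1 more infants, where ρ is the baseline-to-week-4 correlation. ρ is not stated.

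- ρ = 0.2: 1/0.96 − 1 = 4%.
- ρ = 0.5: 1/0.75 − 1 = 33%.

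**The case against.** **The article is condensed.** Multiplicity rules, a lead marker and the ranking of analyses are commonly left to an SAP, which is not shown. This stands in part: the missing correction alone would not be a finding. It does not remove the conflict between Objectives and Primary outcomes, which are two statements in the same document. Nor does it remove the stated commitment to test every marker at every visit, baseline included.

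**The mixed-effects model.** A reader might infer that the primary analysis consists of the 16 rank tests and that baseline is ignored. The document does not support that. The same item plans a repeated-measures model, baseline is one of its listed visits and may enter as a repeated measurement, and the covariate list is open. What remains is that neither analysis is decisive and the enrolment value is not named as a covariate.

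**The size of the error.** A reader might infer that a false claim is close to a coin toss. That needs nearly independent tests, and the 56% figure also counts baseline tests that cannot support a claim. Every figure further presumes that any p<0.05 counts as success, a rule the document does not state for objective 2.

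**Precision.** The Mann–Whitney test is valid under randomisation and a defensible choice for ELISA concentrations. iFABP power is already about 97%, and at ρ = 0.2 adjustment gains only 4%. No consequential loss of precision is shown.

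**Conclusion.** The point holds in this form: the visit for objective 2 is stated in two incompatible ways, and the outcome is spread over four markers and four visits without a designated visit, marker or analysis. It carries no stated error control, although the article states such control for lesser outcomes. If any nominal p<0.05 were taken as success, the chance of a false positive would be 27–46% over the 12 post-baseline tests, or 13–19% over the four week-4 tests. Both ranges rest on assumed correlations of 0.7 to 0 between markers and between visits, and on two-sided 0.05 applying to this item.

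This is a should-fix. It affects what can be claimed for objective 2; it does not affect the sample size, the sampling schedule or the validity of the week-4 data.

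**What to change.** - Reconcile Objectives and Primary outcomes by making week 4 the sole primary visit for objective 2.
- Make one analysis decisive: log marker at week 4 regressed on arm, adjusted for the infant's enrolment value and sex. Keep the Mann–Whitney test as a sensitivity analysis.
- Apply Holm across the four markers. Alternatively, name iFABP, the marker that was sized, as sole primary and make the other three secondary.
- Drop the between-arm tests at baseline.
- Make weeks 7 and 36 secondary, with Benjamini–Hochberg.

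Cost: wording in the protocol and SAP, with no extra samples or infants. No interim analysis is planned and the trial is blinded, so the change can be made before unblinding. Under Holm, iFABP power drops from about 97% to about 91% at the first step; the cost for the other three markers is unknown. With iFABP as sole primary, its power is not reduced, but the other three markers no longer carry a primary claim.

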### Sample size

We propose to enrol 200 iHEU based on sample size calculation conducted for each of the three primary objectives.Objective 1: Sample size calculations were based on metagenomic data from D’Souza et al. (2020) [44], and on *B. infantis* copies in the stool collected at day 4–7 of life from infants in our current observational cohort from the same clinical site, where the mean *B. infantis* copy number was 3000 per 2.5 ng gDNA. The power analysis was based on a generalized linear regression approach, with a betabinomial error model for the dependent variable where varying effect sizes were injected to calculate effective power. The sample size of 100 iHEU per group is adequately powered to detect a difference of at least twofold for differential abundance testing and R^2^ values of 0.01 or higher in PERMANOVA analyses between iHEU administering *B. infanti*s Rosell®-33 versus those administering placebo, even after accounting for a lost-to-follow-up rate of 9% at week 36 (based on our observational cohort).Objective 2: Based on data from our observational cohort where the mean log intestinal fatty-acid binding protein (iFABP) plasma concentration in iHEU at day 4–7 was 0.454 ng/ml with a standard deviation of 0.164, we will have 80% power to detect a 20% difference in iFABP with *n* = 51 per group. Therefore, our proposed sample size of *n* = 100 per group will be ample to detect what we think is a meaningful difference.Objective 3: A sample size of 78 per group (total *n* = 156) will provide 80% power to detect a 45% increase in total net Th1 cytokine responses to BCG based on preliminary data in iHEU where the mean response was 0.78 and standard deviation 0.8, and the proposed sample size of 100 iHEU per arm accounts for a predicted loss-to-follow-up rate of 2.5% to 7 weeks, resulting in an expected sample size of *n* = 195 at week 7.

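### On the natural reading, the ROC accuracy of the BCG functional-profile model is scored on the same infants used to select and fit it, so any AUC reported is too high

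*Protocol article*

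**What the plan says.** The protocol article, Primary outcomes, third item, first compares total net cytokine-producing cells between arms by adjusted linear regression. It then adds a COMPASS analysis in fixed steps:

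1. A functionality or polyfunctionality score is regressed on arm: "We will perform two-sided hypothesis testing with alpha = 0.05".
2. If that test gives p < 0.05, "we will perform a series of univariate analyses in which we test for an association between a particular functional profile and arm".
3. "Those profiles identified as significantly associated will be incorporated into a multivariate linear regression model, which will include two-way interaction terms". The stated aim is exploratory in character: "This will allow us to create a model that includes the cytokine-producing profiles that are most associated with the intervention".
4. "We will test the classification accuracy of this model using receiver-operative curve (ROC) analysis".
5. "In all models, we will include sex, birth weight, and feeding mode as possible confounders".

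The section names no hold-out set, cross-validation, bootstrap or second cohort. The Sample size section gives the data available at that visit: "resulting in an expected sample size of *n* = 195 at week 7". False-discovery-rate control is stated for taxa and functional genes, for metabolites and for the qPCR comparisons, but not for the profile screen in step 2.

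**The concern.** The profiles enter the model because they differ by arm in these infants. The coefficients, including those of the interactions, are then tuned to the same infants. If the ROC curve is drawn from the same infants again, it counts chance differences as discrimination. The resulting AUC describes how well the model fits its own data, not how well BCG profiles distinguish supplemented from unsupplemented infants.

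The analysis stands under a primary outcome and carries no exploratory label. A reader could therefore take a high AUC as support for an immunological effect, or as a measure of how strong that effect is.

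**Working it through.** **The plan's own figure.** 200 infants with 2.5% lost by week 7: 200 × (1 − 0.025) = 195. This reproduces the stated number. The article states no AUC, so the check is a simulation of the steps as written.

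**Inputs from the article.** 195 infants allocated 1:1 (97 and 98); two-sided 0.05 for the score test; univariate screen, with 0.05 taken as its threshold too; all two-way interactions among selected profiles; sex, birth weight and feeding mode in the model.

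**Assumptions not in the article.** 7, 15 or 31 profiles; normal data with equal between-profile correlation of 0, 0.3 or 0.6; the mean of the profiles as a stand-in for the COMPASS score; arm as the dependent variable of the final model; simulated covariates unrelated to arm.

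**Model size.** With k selected profiles the model has k + k(k − 1)/2 + 3 terms besides the intercept:
- k = 3: 3 + 3 + 3 = 9
- k = 7: 7 + 21 + 3 = 31
- k = 12: 12 + 66 + 3 = 81

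**No product effect.** There were 250 completed runs per setting, each with the score test passed and at least one profile selected. The apparent AUC is scored on the fitting infants. The fresh AUC applies the same fitted model to 2000 new infants. The cross-validated AUC is 10-fold, with screen and fit repeated in each fold. The true value is 0.50.

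| Profiles | Correlation | Null trials passing score test | Median selected | Apparent AUC, mean (5th–95th percentile) | Fresh AUC | Cross-validated AUC |
|---|---|---|---|---|---|---|
| 7 | 0 | 5.3% | 1 | 0.632 (0.60–0.68) | 0.500 | 0.518 |
| 7 | 0.3 | 5.7% | 2 | 0.645 (0.60–0.69) | 0.500 | 0.530 |
| 7 | 0.6 | 4.7% | 3 | 0.657 (0.61–0.72) | 0.500 | 0.535 |
| 15 | 0 | 4.5% | 1 | 0.642 (0.59–0.71) | 0.500 | 0.510 |
| 15 | 0.3 | 4.9% | 3 | 0.678 (0.61–0.77) | 0.500 | 0.525 |
| 15 | 0.6 | 5.1% | 6 | 0.736 (0.64–0.90) | 0.500 | 0.540 |
| 31 | 0 | 5.0% | 2 | 0.665 (0.59–0.75) | 0.500 | 0.503 |
| 31 | 0.3 | 5.2% | 7 | 0.764 (0.66–0.94) | 0.498 | 0.544 |
| 31 | 0.6 | 4.9% | 12 | 0.881 (0.73–1.00) | 0.500 | 0.523 |

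The three covariates alone, fitted and scored on the same infants, gave about 0.56.

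**Does the score test remove the bias?** No. With 15 profiles and correlation 0.3, the mean apparent AUC was 0.630 without the score test (runs with at least one profile selected) and 0.678 with it.

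**With a true effect** (15 profiles, correlation 0.3, the same shift in every profile). The larger shift is the planned one for this objective: 0.45 × 0.78 = 0.351, and 0.351 / 0.8 = 0.44 SD.

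| Standardized shift | Apparent AUC | Fresh AUC | Cross-validated AUC |
|---|---|---|---|
| 0.2 | 0.737 | 0.553 | 0.545 |
| 0.44 | 0.934 | 0.567 | 0.561 |

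The optimism is 0.737 − 0.553 = 0.18 and 0.934 − 0.567 = 0.37. Cross-validation lands close to the fresh-infant value in both cases.

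**The case against.** **Scoring on the same infants is inferred.** The article condenses a fuller protocol, and the analysis plan is not shown. Either could specify cross-validation. This stands as a limit on certainty. But the article sets out the score test, screen, interactions, covariates and accuracy measure in order, and the ROC sentence refers back to the model just built. Followed as written, the steps give an optimistic figure.

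**The score test shields most null trials.** This also stands. A reader might infer that an ineffective product would usually yield an impressive AUC. It would not: about 95% of null trials stop before the ROC step with one score, somewhat fewer if either of two scores may open it. What the score test does not do is correct the AUC in the trials that go on.

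**The profile screen is not wholly unprotected.** A global test before the individual ones limits false profile claims when no profile differs at all. It gives no such control once some profiles truly differ. So it would go too far to say that the screen has no multiplicity protection.

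**The linear model is not the source of the bias.** A reader might object to a linear regression for a two-level outcome. The article does not name the dependent variable, and AUC depends only on the ranking of the fitted values. No bias from this choice was shown.

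**The size rests on assumptions.** The number and correlation of profiles are not in the article, and the score was approximated. The direction was the same in every setting tried; the amount is supported only as a range.

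**Conclusion.** The point holds as a bias in an additional analysis. On the natural reading, the AUC is too high whenever it is reported, whether or not the product works. With no effect, and given that the ROC step is reached, the mean apparent AUC is about 0.63 to 0.88 against a true 0.50, for 7 to 31 profiles and correlations of 0 to 0.6. With a true effect, the model's discrimination is still overstated.

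A reader might infer that the third primary outcome itself is compromised. The article does not support that: the between-arm regression of total net Th1 responses, on which the sample size for this objective rests, does not use the selected model. Nor does the article say that the AUC will be offered as evidence of efficacy. The point should be settled before week-7 data are analysed, but it does not threaten the main comparison.

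**What to change.** Replace the ROC sentence with an AUC from cross-validation or bootstrap in which the profile screen, the interactions and the fit are all repeated inside each resample, and label the result exploratory.

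Preferably add a permutation p-value that reshuffles arm and reruns the whole sequence, including the initial score test. In the null simulations, cross-validation with the score test left outside the folds still gave 0.50 to 0.54. The permutation reference takes in that small excess.

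Applying Benjamini–Hochberg to the profile screen, as the plan already does for taxa, is a reasonable optional addition. Changing from linear to logistic regression is not needed to remove the bias.

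The cost is slightly more analysis code and a lower reported AUC. Data collection, sample size and trial conduct do not change.
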